## 8. Data Collection and Analysis

### 8.1. Data Collection

The data collection plan has been meticulously designed to guarantee the quality, integrity, and confidentiality of the data collected throughout the randomized clinical trial. The study coordinator will oversee data management and assume responsibility for specific tasks following the collection of paper-based records. Subsequently, encrypted Excel databases will be created to maintain participant confidentiality by implementing a double-entry procedure to ensure the integrity and accuracy of the records. Key methodological aspects, including the sample size, eligibility criteria, randomization, blinding procedures, treatment, and outcome variables, will be precisely defined and detailed in the methodology section of the study. Data will be collected using standardized record forms and electronic systems, with a rigorous protocol for eliminating incomplete entries, to ensure data consistency and reliability at the conclusion of the trial.

### 8.2. Statistical Analysis

#### 8.2.1. Baseline Characteristics

For the comparison of the results between groups, inferential analysis will be conducted using a repeated measures ANOVA or chi-square tests to determine whether there is a significant relationship between two categorical variables.

#### 8.2.2. Analysis of the Outcome Measures

The assumption of normality will be evaluated using the Kolmogorov–Smirnov test, while the homogeneity of variances will be assessed with Levene’s test. A two-way mixed-design ANOVA will be employed, with the time serving as the within-subject factor and the treatment group as the between-subject factor. Tukey’s post hoc correction will be applied to examine the effects of both the primary and secondary outcomes. The results will be presented as the mean differences (MDs) with 95% confidence intervals (CIs). The effect sizes (ESs) will be calculated using Cohen’s d. In the event of participant dropouts during the study, or if the statistical power falls below the predetermined threshold of 80%, an intention-to-treat analysis will be conducted [62]. All the statistical analyses will be conducted by an independent researcher who will not be involved in the data collection and will utilize anonymized, coded datasets.

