## 3. Randomization and Blinding

The principal investigator, supported by a team of experienced physiotherapists with over a decade of expertise in neuromodulation and exercise therapy for UI, will oversee the implementation of the treatment protocol. Stratified randomization will be employed to ensure that the groups being compared are balanced in terms the specific levels of OAB-q SF [25]. The baseline OAB-q SF levels will be assessed before randomization, and the participants will be divided into two strata according to these levels, as outlined in the corresponding sections. One of the researchers will administer the interventions across all three groups, while the other will conduct the outcome assessments to maintain evaluator blinding. A block randomization design (block sizes of 4, 6, or 8) will be applied to ensure an equal number of participants in each group. To minimize the bias, the group allocation will be determined using a randomization table generated by an independent researcher using Excel. A double-blind design will be implemented to ensure objectivity.

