## 4. Sample Size

Statistical analysis was performed using a repeated measures analysis of variance (ANOVA), focusing on the primary variable, OAB-q SF. Drawing on a previous study on transcutaneous tibial nerve stimulation in women with idiopathic overactive bladder [26], the Cohen’s effect size was estimated to be 1.04. The statistical power was set at 0.80, with an alpha level of 0.05, considering the three intervention groups. Initially, 54 individuals were allocated to three groups (18 participants per group). To account for a potential 15% dropout rate during follow-up, three additional participants were added to each group, resulting in 21 participants per group and a total sample size of 63. The required sample size was calculated using G*Power software (version 3.1.9.2; Franz Faul, Universität Kiel, Kiel, Germany).

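### The primary ANOVA leaves out the baseline OAB-q SF and the strata already collected, and ties no test to the 12-week objective: it is valid but loses precision

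*Protocol article*

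**What the plan says.** The model is fixed in section 8.2.2 of the protocol article: "A two-way mixed-design ANOVA will be employed, with the time serving as the within-subject factor and the treatment group as the between-subject factor". The same section adds Tukey's correction, mean differences with 95% confidence intervals and Cohen's d. None of these is attached to a visit or to a pair of arms.

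Four other places bear on it:

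- Section 2.4 sets four measurements: baseline and 1, 3 and 6 months. The Discussion explains these follow-up times but does not rank them.
- Section 3: "The baseline OAB-q SF levels will be assessed before randomization", and participants are then split into two strata on that score.
- The Introduction sets the objective after 12 weeks of treatment, comparing the combination with sham plus exercise or with conventional physiotherapy.
- Section 4 sizes the trial "focusing on the primary variable, OAB-q SF".

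Section 8.2.1, headed as baseline characteristics, says that "inferential analysis will be conducted using a repeated measures ANOVA or chi-square tests".

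**The concern.** The trial measures its own primary outcome before randomisation and stratifies on it. The stated model then has two factors only, and neither carries that information as a covariate. With baseline as a time level, three things follow:

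- The group main effect averages in a pre-treatment visit, at which randomised arms do not differ in expectation.
- The group-by-time interaction is a joint test over all visits. Rejecting it does not show benefit at 12 weeks or over a particular comparator.
- The month-3 comparison inside this model is in effect a difference in change from baseline, which is less precise than a baseline-adjusted difference.

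At stake is precision in a trial that expects about 18 evaluable women per arm, and clarity about which result answers the 12-week question. Bias is not at stake.

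**Working it through.** **Inputs from the protocol article.** Three arms, 1:1:1; four measurement times. Section 4 gives the effect size ("the Cohen’s effect size was estimated to be 1.04"), 5% alpha, 80% power, 18 evaluable women per arm (54 in all) and a 15% dropout allowance that adds three per arm.

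**Assumptions.** Two-sided 5% tests. Common SD at all visits, with 1.04 read as a difference between two arms in units of that SD. Correlation rho between baseline and month 3, taken as 0.3 to 0.8. Month 3 taken as the end of the 12 weeks.

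**The plan's own figure.** Two arms, d = 1.04, 80% power: n per arm = 2 × (1.96 + 0.84)² / 1.04² = 14.5, so 15, or 16 with the t distribution. Three arms give 45 to 48, not 54. Choices that the article does not state can produce 54. That is a separate matter, and nothing below depends on it: 18 per arm is taken as given. The allowance to 21 follows from 18 × 1.15 = 20.7.

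**What the omnibus tests address.** With a constant effect, the main-effect difference is (0 + 1 + 1 + 1)/4 = 0.75 of it. The interaction has (3 − 1) × (4 − 1) = 6 degrees of freedom.

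**Variance of the month-3 contrast**, in units of SD² × 2/n:

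- change from baseline: 2(1 − rho)
- baseline-adjusted (ANCOVA): 1 − rho²
- ratio: (1 + rho)/2, so the saving is (1 − rho)/2

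With n = 18, sqrt(2/18) = 0.3333. The detectable difference is 2.80 × SE (80% power, one pairwise contrast, uncorrected).

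| rho | SE, change | SE, adjusted | Variance saved | Detectable, change | Detectable, adjusted |
|---|---|---|---|---|---|
| 0.3 | 0.394 | 0.318 | 35% | 1.11 SD | 0.89 SD |
| 0.5 | 0.333 | 0.289 | 25% | 0.93 SD | 0.81 SD |
| 0.7 | 0.258 | 0.238 | 15% | 0.72 SD | 0.67 SD |
| 0.8 | 0.211 | 0.200 | 10% | 0.59 SD | 0.56 SD |

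**Power for the same pairwise contrast**, 1.04 SD, rho 0.5, error pooled over three arms (51 and 50 degrees of freedom). The noncentralities are 1.04/0.333 = 3.12 and 1.04/0.289 = 3.60.

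- Uncorrected (critical value 2.01): about 86–87% for change and 94% adjusted, a gain of about 7 to 8 points.
- Tukey, three arms (critical value 2.41): about 76% and 88%, a gain of about 12 points.

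**Are the omnibus tests always weaker?** No. These are simulated powers with 18 per arm, equal correlations, one arm shifted by 0.8 SD and 2,000 replicates. The comparator is a two-degree-of-freedom ANCOVA at month 3.

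- rho 0.5, effect peaking at month 3: main effect 0.28, interaction 0.50, ANCOVA 0.79.
- rho 0.5, sustained effect: 0.62, 0.70, 0.79.
- rho 0.7, sustained effect: interaction 0.93, ANCOVA 0.92.
- rho 0.3, sustained effect: main effect 0.74, ANCOVA 0.71.

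The better omnibus test therefore depends on rho and on the shape of the effect. Both are unknown, and the article does not choose between the tests.

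**The case against.** The strongest reply is that a mixed-design ANOVA is a legitimate analysis of a randomised design with a pre-treatment measurement. It neither biases the comparison nor inflates the type I error. That stands, and the point is one of efficiency and focus.

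A second reply is that an article may leave covariates and the exact contrast to an analysis plan that is not shown, and that Tukey comparisons could include month 3. This stands in part. A 12-week comparison is possible, so it would be wrong to infer that none can be made. But the article does state the model, and that model has two factors and no covariate. That baseline is a time level is inferred from sections 2.4 and 8.2.2 together; it is not stated outright.

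A reader might also infer more than the documents support:

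- **A large power gap.** With 1.04 SD at month 3, half that at months 1 and 6, and rho 0.5, simulation gives 49% for the main effect, 76% for the interaction and 94% for one adjusted contrast. These tests ask different questions, and the 94% carries no multiplicity correction. Like for like, baseline adjustment is worth 7 to 12 points.
- **A saving that grows with rho.** Against a month-3 score taken alone, the saving is rho², or 49% at rho 0.7. If baseline is a time level, the relevant comparator is change from baseline, and the saving is 15%.
- **An inflated error term from omitting the strata.** This applies to the group main effect only. The subject term already removes a constant stratum effect from the interaction, and stratum probably adds little once continuous baseline is in the model.
- **Planned significance tests of baseline.** Section 8.2.1 is ambiguous: its sentence speaks of comparing results, under a baseline heading.

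**Conclusion.** The point holds as a loss of precision and a lack of focus in a valid, unbiased analysis. For the month-3 contrast, adjustment is more precise than change from baseline at every rho below 1. The size rests on a correlation that the documents do not give, on a common SD, and on reading baseline as a time level. The gain is moderate at low to middling correlations and small at rho 0.8. No general claim that the omnibus tests lack power is justified. The change is worth making because the data are already being collected, but the trial does not fail without it.

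**What to change.** In section 8.2.2, replace the two-way ANOVA for the primary outcome with a mixed model (or ANCOVA) of post-baseline OAB-q SF. Include baseline OAB-q SF, randomisation stratum, group, visit and group-by-visit. Name as primary the month-3 (end of 12 weeks) differences of neuromodulation versus sham and versus conventional physiotherapy, each with a 95% confidence interval and the planned multiplicity correction. Both comparisons belong there because the stated objective names both; reporting sham alone would narrow it.

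As a minor separate edit, reword section 8.2.1 so that baseline is described by arm rather than tested. Repeated measures ANOVA cannot apply to a single visit.

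The cost is wording in the protocol and analysis plan, settled before unblinded analysis. No new data, visits or participants are needed.

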### 2.4. Procedure

Once the groups have been assigned, four sample collections will take place at the following time points: Pre (baseline), Post_1month_, Post_3months_, Post_6months_ (Figure 2). All the participants will engage in 24 experimental sessions, each with a duration of approximately 60 min. At each assessment point, the studied variables will be monitored and recorded in the “Data Collection Notebook”. It has been created to systematically record both the primary and secondary outcome variables at each measurement point, in alignment with the study protocol.

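### The four-visit mixed ANOVA is specified down to its assumption checks without a sphericity check or correction, so its group-by-time test can run above 5% (minor)

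*Protocol article*

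**What the plan says.** Section 8.2.2 (Analysis of the Outcome Measures) names the model: "A two-way mixed-design ANOVA will be employed, with the time serving as the within-subject factor and the treatment group as the between-subject factor". It then goes down to individual assumption checks: "The assumption of normality will be evaluated using the Kolmogorov–Smirnov test, while the homogeneity of variances will be assessed with Levene’s test". It also fixes the multiplicity step: "Tukey’s post hoc correction will be applied to examine the effects of both the primary and secondary outcomes". Results are to be given as mean differences with 95% confidence intervals.

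Section 2.4 (Procedure) says that "four sample collections will take place at the following time points" and lists baseline and 1, 3 and 6 months. Section 4 (Sample Size) gives the error rate: "The statistical power was set at 0.80, with an alpha level of 0.05, considering the three intervention groups". It plans 18 participants per group before dropout and 21 after.

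The article does not mention sphericity, Greenhouse-Geisser or Huynh-Feldt. It gives no correlation between visits, no covariance and no epsilon.

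**The concern.** With four visits, the F tests for time and group-by-time use their nominal degrees of freedom correctly only under sphericity, which means that differences between any two visits all have the same variance. Neither listed check addresses this. Levene's test compares variances between groups, and the Kolmogorov–Smirnov test looks at the shape of the distribution. An analyst who worked through the list would check two assumptions and miss the one specific to repeated measures.

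Repeated questionnaire scores are often more alike at close visits than at distant ones. In that case the uncorrected F tests use too many degrees of freedom and err towards rejection. The group-by-time test matters here because the group main effect averages over all four visits, baseline included, whereas the interaction asks whether the arms change differently. If the correction is not fixed in advance, someone could also choose between corrected and uncorrected p-values after seeing the data, and that choice could decide a borderline result.

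**Working it through.** **Inputs from the article.** 3 groups; 4 visits at 0, 1, 3 and 6 months (section 2.4); 18 per group before dropout and 21 after (section 4); alpha 0.05 (section 4).

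**Assumed inputs.** The covariance between visits, since the article gives none. A range is shown.

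**Degrees of freedom.** For group-by-time, (3 − 1)(4 − 1) = 6 and (54 − 3)(4 − 1) = 153. The uncorrected 5% critical value is F(6, 153) = 2.158.

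**Epsilon.** Let A be the 3 × 3 covariance matrix of the orthonormal contrasts between visits. Then ε = (tr A)² / (3 · tr A²). ε = 1 is sphericity, and 1/3 is the lower bound with four visits. When ε < 1, the F statistic behaves approximately as F(6ε, 153ε), so the true error rate is approximately P[F(6ε, 153ε) > 2.158].

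**Worked case: correlation 0.8 per month, equal variances.** The correlation at a lag of L months is 0.8^L. The variance of a difference between visits, in units of the outcome variance, is 2(1 − 0.8^L). From baseline to month 1 it is 2(1 − 0.8) = 0.40. From baseline to month 6 it is 2(1 − 0.262) = 1.476. These are unequal, so sphericity fails in this case. Here tr A = 1.473 and tr A² = 0.985, so ε = 1.473² / (3 × 0.985) = 2.170 / 2.955 = 0.73. The degrees of freedom become about 4.41 and 112.4, and the error rate is about 7.2%.

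**Plan's own figure first.** Under compound symmetry (all correlations equal, equal variances) ε = 1, and the simulated rate is 4.9% to 5.1%. The stated 5% is reproduced.

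**Range of assumptions** (uncorrected test, 18 or 21 per group, mostly 40,000 simulated null trials per case; standard error about 0.1 percentage points):

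| Assumed covariance | ε | Approximation at 18 per group | Simulated |
|---|---|---|---|
| Compound symmetry | 1.00 | 5.0% | 4.9–5.1% |
| Compound symmetry, SDs rising from 1 to 1.5 | 0.95 | – | 5.1–5.3% |
| 0.7 per month | 0.80 | 6.6% | 6.0–6.5% |
| 0.8 per month | 0.73 | 7.2% | 6.9–7.4% |
| 0.9 per month | 0.67 | 7.9% | 7.5–8.0% |
| 0.7, 0.8 or 0.9 per month, plus independent measurement error (reliability 0.8) | 0.86–0.89 | 5.9–6.0% | 5.5–6.1% |
| Baseline–post 0.4, post–post 0.7 | 0.82 | – | 6.2–6.4% |
| Theoretical worst case | 0.33 | – | 12.8% |

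If the Post months are counted from the end of the 12-week treatment (visits at about 0, 4, 6 and 9 months), the serial patterns give 5.4% to 6.7%. The worst case is a mathematical bound and not a realistic scenario.

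**With the correction.** The Greenhouse-Geisser test stays between about 4.5% and 5.3% in every case.

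**The case against.** The strongest reply is that this is a silence and not an error. The article condenses a longer plan, the SAP is not shown, and naming two checks does not exclude a third. A reader might infer that the test definitely will be uncorrected and definitely exceeds 5%. The documents do not support that: they never say that a correction will be omitted, and they give no covariance from which to conclude that sphericity fails. Unequal visit spacing alone does not prove failure, and under compound symmetry the rate is 5%. This part of the objection stands, and it is why the point is conditional.

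The size also depends on the covariance family. Pure serial decay with no measurement error is unfavourable: at 0.7 per month it implies a baseline-to-month-6 correlation of only 0.7^6 = 0.12. The primary outcome is a self-administered questionnaire, so some visit-specific error is to be expected. With a reliability of 0.8 (assumed), the excess shrinks to about one percentage point. This stands too.

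Finally, section 8.2.2 does not name the group-by-time F test as decisive, and it reports mean differences with Tukey-adjusted comparisons. The calculations cover only the overall interaction test and show nothing about those contrasts. That limits the reach of the point.

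One thing survives all of this. The section does not stop at naming ANOVA. It lists the assumption checks, and the list leaves out the one on which the within-subject tests of the chosen model rest.

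**Conclusion.** The point holds in conditional form and is minor. If the mixed ANOVA is run with only the listed checks, and correlations fall with the time between visits, the group-by-time type I error can exceed 5%. It is about 5.5% to 8% under the assumed serial patterns and nearer 6% with measurement error. If sphericity holds, there is no inflation. These rates rest on assumed covariances and on no correction being applied, and the documents establish neither. Non-sphericity makes the uncorrected overall test too liberal, and the same issue would arise for every continuous outcome put through this model.

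**What to change.** Add one sentence to section 8.2.2: the Greenhouse-Geisser correction is applied by default to all within-subject tests (time and group-by-time), whatever a preliminary sphericity test shows.

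Alternatively, replace the mixed ANOVA with a mixed model for repeated measures with unstructured covariance, Kenward-Roger degrees of freedom, and the baseline OAB-q SF score and randomisation stratum as covariates. The unstructured covariance removes the need for sphericity. The covariates do not bear on sphericity; they use information that the trial already collects for its stratified randomisation.

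Either choice leaves visits and data collection unchanged. The cost is slightly larger p-values when ε is below 1, and a little programming. The first option is enough to close this point.

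If an SAP already names a correction, a matching sentence in the protocol is all that is needed.

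### Intention-to-treat is a contingency triggered by dropout or low power, not the stated primary analysis, and the planned ANOVA and the rule on incomplete entries pull against it

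*Protocol article*

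**What the plan says.** Section 8.2.2 of the protocol article sets the outcome model: "A two-way mixed-design ANOVA will be employed, with the time serving as the within-subject factor" and treatment group as the between-subject factor. Section 2.4 fixes the number of levels of time: "four sample collections will take place at the following time points", namely baseline and 1, 3 and 6 months.

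The same part of section 8.2.2 gives two triggers for ITT. One is any dropout during the study. The other is low power: "if the statistical power falls below the predetermined threshold of 80%, an intention-to-treat analysis will be conducted". It does not say which participants are analysed if neither trigger is met, or whether the triggered ITT is the primary analysis.

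Section 8.1 describes data collection as proceeding "with a rigorous protocol for eliminating incomplete entries, to ensure data consistency and reliability at the conclusion of the trial".

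Section 4 names the OAB-q SF as the primary variable. It sets power at 0.80 and alpha at 0.05, and raises 54 participants to 63 for an expected 15% dropout.

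**The concern.** Analysing everyone in the arm to which they were randomised is a principle to settle before the data exist. Here it is a response to events during the trial, and three things follow.

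- **The power trigger has no sound basis.** ITT is not a remedy for low power. If power is judged from the observed effect, the analysis set depends on the result.
- **The triggers do not address adherence.** Section 6 says efficacy may fall substantially when compliance is below 80%. A woman who attends poorly but stays in follow-up is not a dropout, so her case triggers nothing. The ITT would reach her only if someone else drops out or power is judged low.
- **The surrounding text works against the ITT once it is triggered.** In its conventional form, a mixed-design ANOVA needs every participant to have all four measurements. A rule that eliminates incomplete entries can be read the same way. A woman with a valid 3-month OAB-q SF score who misses month 6 could then leave the analysis altogether.

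At stake is the protection that randomisation gives to the primary comparison. If dropout is related to response and differs between arms, comparing completers is biased.

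**Working it through.** **Inputs.** 54 participants (18 per group) before and 63 (21 per group) after a 15% dropout allowance; power 0.80; alpha 0.05 (all section 4). Four measurement points (section 2.4). Model and triggers from section 8.2.2; elimination rule from section 8.1.

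**1. The plan's dropout allowance.** 18 × 1.15 = 20.7, rounded up to 21 per group, so 63 in total. The stated figure reproduces. Dividing instead, 54 / 0.85 = 63.5, rounded up to 64. That difference of one does not affect this point.

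**2. How often the dropout trigger fires.** With independent dropouts at rate q, P(at least one of 63) = 1 − (1 − q)^63.

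| q | P(at least one dropout) |
|---|---|
| 15% (planned) | 99.996% |
| 5% (assumed) | 96% |
| 2% (assumed) | 72% |

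Under the plan's own assumption the ITT is triggered almost always, and the power trigger decides alone only if nobody drops out.

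**3. Who a complete-case ANOVA keeps.** At 15% dropout, 63 × 0.85 = 53.55 remain and 63 × 0.15 = 9.45 are left out, about 9 to 10 women. Intermittent missed visits would add to this. Assume independent missingness m at each of the three follow-up visits and a complete baseline, so that 63 × (1 − m)^3 have all four scores:

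| m (assumed) | Complete on all four visits |
|---|---|
| 5% | 54 |
| 10% | 46 |
| 15% | 39 |

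**4. What the power trigger can mean.** The article does not define it.

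- *Power at the retained sample size.* With 63 recruited, falling below the planned 54 takes at least 10 losses (63 − 10 = 53). If these are dropouts, the first trigger has already fired, so the second adds nothing. ITT would also be serving as a remedy for lost numbers, which it is not.
- *Observed power.* The trigger then follows the observed effect. As a simplification to a two-sided, two-group z test, observed power of 80% corresponds to z = 1.960 + 0.842 = 2.80, or p of about 0.005. In a simulation of a two-group t test with a true standardised difference of 1.04, observed power fell below 80% in about 40% of trials at 18 per group and 31% at 21 per group. Neither figure is for the planned three-group, four-visit ANOVA.

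**5. Possible bias from analysing completers (assumed inputs).** If dropouts would score D worse than completers, the completers' mean in an arm with dropout rate p is too favourable by p × D. The contrast between arms A and B is then biased by (pA − pB) × D.

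| pA | pB | D | Bias |
|---|---|---|---|
| 15% | 15% | 1 SD | 0 |
| 25% | 5% | 0.5 SD | 0.10 SD |
| 25% | 5% | 1 SD | 0.20 SD |

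The documents give no dropout rate by arm and no value of D, so this is a range and not an estimate.

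**The case against.** The strongest reply is that the dropout trigger alone makes an ITT almost certain, whatever the result, and that the article defines no per-protocol set and no exclusion for poor adherence. This stands. A reader might infer that the population will be chosen after seeing the result and that the p-value is therefore uninterpretable. The documents do not support that: the power trigger acts alone only if nobody drops out, and observed power is only one reading of it.

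A reader might also infer that ITT cannot be done with the stated ANOVA. That is too strong. The ANOVA can include every randomised participant once missing visits are imputed. The method may be in the full protocol or an analysis plan that is not shown, and its absence from an article is not a fault.

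The incomplete entries of section 8.1 appear among paper records, databases and double entry. They may be unfinished data records and not participants, so removal of participants is one reading and not stated text.

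Finally, differing treatment burden is a less certain source of unequal dropout than it looks. The active and sham arms both combine exercise with a needle procedure. For the control arm, section 4.1.3 gives 8–12 sessions of 20–40 minutes, while section 2.4 gives every participant 24 sessions of about 60 minutes. Those passages need reconciling before burden can be compared.

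None of this removes the conditional wording, the invalid power criterion, the unstated status of the ITT or the tension with section 8.1. If ITT is in practice always intended, the condition serves no purpose.

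**Conclusion.** The point holds as a fault in what the article states. ITT is conditional, one of its two conditions is not a legitimate reason to choose an analysis set, and the analysis is not designated primary. Because dropout makes the ITT almost certain, the main practical risk lies in its execution. Applied in their plainest form, the four-visit ANOVA and the elimination rule would leave out about 9 to 10 of the 63 randomised women at the planned 15% dropout, and more if visits are also missed intermittently.

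That count assumes a conventional complete-case ANOVA with no imputation. Any resulting bias cannot be sized from the documents. On the assumed inputs above it runs from zero with equal dropout to 0.20 SD with 25% against 5% dropout and a 1 SD deficit. No sample-size or alpha figure changes.

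**What to change.** 1. In section 8.2.2, state without condition that the primary analysis includes all randomised participants in the arm to which they were allocated.
2. Delete both the dropout trigger and the power trigger.
3. Analyse all observed OAB-q SF scores with a method that keeps participants who have missing visits. A linear mixed model with categorical time would do this. So would the stated ANOVA after multiple imputation.
4. Reword section 8.1 so that incomplete records are queried and retained, and make clear that the rule concerns data records and does not remove participants.
5. Report completers only as a sensitivity analysis.

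The cost is an amendment to the wording and a standard statistical procedure. No extra patients, visits or measurements are needed. The change should be made before anyone sees outcomes by arm.
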